### Interventions

#### Quitline-based treatment (QT group)

Participants in the QT group will receive standard proactive quitline services from China Professional Quitline ([name]) for 4 weeks using a multi-call quitline protocol [19]. The first session will focus on quitting history, motivation, self-efficacy, social support, and planning in advance of the quitting date. Smokers will be reminded in the second session to quit smoking completely from the quitting date, be provided with the practical information on how to quit. The sessions followed the quitting date (up to three sessions) will focus on building cessation skills and relapse prevention. Three Chinese-speaking counselors will provide the quitline services. All of them possess at least a bachelor’s degree in medicine or nursing, and have received more than 60 h of training in smoking cessation counseling.

To improve the participants’ adherence of the quitline intervention protocol, the counselors will call them at three time points for three consecutive days during each session, arrange the next session time for the participants, and contact the participants’ relatives and friends whenever necessary.

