Week 3	Maintenance	Coping with smoking craving	You may feel depressed after quitting smoking. Please do some things to make yourself happy, such as calling your best friends, watching movies, and shopping, etc	Skills to cope with smoking craving	How did I cope with smoking craving?	Sharing quitting achievements picture in the online group	Recording quitting Benefits from quitting Coping with cravings
Week 4	Maintenance	Preventing relapse	Refuse accidental smoking! The most difficult period is almost over	How to prevent relapse	What benefits do I get from quitting smoking?	Sharing smoking cessation experience in the online group	Recording quitting Benefits from quitting Quitting tasks

^a^WQ, Way to Quit

^b^WMP, WeChat mini-program

^c^WG, WeChat group

The QUIT WG is an online group chat function embedded in the WeChat app (up to 500 persons), which could offer real-time online cessation counseling, group interventions, and facilitate the formation of mutually reciprocated, strong, and long-lasting social bounds that support smoking cessation in a similar manner to that of Twitter and Facebook [30–32]. Three counselors are arranged to provide online counseling, and a group administrator is arranged to manage the group and encourage participant to send message. Stage-matched online group interventions will be provided via two manners, including video courses on smoking cessation by clinical expert, and Q&A session after the courses and at 12:00 a.m.-13:00 p.m. from Monday to Friday. We also conducted interactive activities, including topic discussion and quit tasks. Table 2 shows a list of weekly topics and examples of group interventions and interactive activities. Moreover, we introduce the "herd effect" model (opinion leader model) into the WQ modality. Herding is a phenomenon by which individuals follow the behavior of others [33]. It has been reported that people tend to emulate opinion leaders (leading sheep) who could influence others’ opinions, attitudes, beliefs, motivations, and behaviors of others [34], and thus can effectively change many behaviors [35–37].Ten self-selected opinion leaders from the participants will be enrolled as the “Quitting Pioneer” to set an example of successful quitter, share experience of smoking cessation, and promote other smokers to participate in interaction activities.

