### Sample size

The sample size calculation is based on the primary aim of comparing biologically verified 7-day PPA between the QT group and the WQ group at the 1-month follow-up. We used the following assumptions: (1) significance level of 0.05 for a two-sided test; (2) statistical power of 90%; (3) biologically verified 7-day PPA at the 1-month follow-up in the QT group is conservatively estimated as 20% based on the data from California Smokers’ Helpline [19]; (4) an increase in abstinence rate of 15% in the WQ group compared with the QT group; (5) a dropout rate of 20%. Considering the random block size (4 or 6), 460 eligible patients (230 for each group) will be required in this study.

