### Statistical analysis plan

All statistical analyses be analyzed and blinded to the intervention assignment by a statistician using SPSS version 22.0 software (SPSS, Inc., Chicago, IL). Data will be presented as mean (standard deviations) for continuous variables with normal distribution; median (inter-quartile range) for continuous variables without normal distribution; and proportions for categorical variables. Baseline characteristics of participants in the intervention and control groups will be compared using Student’s t-test or non-parametric test for continuous variables and Pearson's chi-square or Fisher's exact test for categorical variables.

Multiple logistic regression will be used for between-group comparisons of the primary outcome variable-biochemically validated 7-day PPA at the 1-month follow-up and the secondary outcomes- self-reported 7-day PPA at the 1-, 3-, 6-, and 12-month follow-up and self-reported continuous smoking abstinence from 1-month to 12-month, with odds ratio (OR) and 95% confidence intervals (CI) to assess between-group effects. By intent-to-treat analysis (ITT), participants who are lost to follow-up or refuse to participate in the validation tests will be considered as continuing smokers with no reduction in cigarette consumption compared with baseline. Participants who do not use smoking cessation services after randomization will be excluded from the ITT analysis data set. In addition, we will conduct a per-protocol (PP) analysis of the primary outcome among the participants in the QT group who receive at least one telephone session and those in the WQ group who use the QUIT WMP for at least 20 days and send more than 10 short messages in the QUIT WG. For comparisons of secondary continuous outcomes with non-normal distribution assumptions, Mann–Whitney tests will be conducted. Subgroup analyses will assess the efficacy in participants with different demographics, baseline smoking characteristics, combined chronic diseases, and use of intervention variables (including compliance of using NRT gum, frequency and duration of using WeChat- or quitline-based cessation services) using multiple logistic regression. No interim analysis will be conducted. A two-sided *P* value of < 0.05 will be considered as statistically significant difference.

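### The per-protocol set asks for one call in QT but 20 days of use plus more than 10 messages in WQ, so its comparison can be expected to lean toward WQ

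*Protocol article*

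**What the plan says.** The Statistical analysis plan section of the protocol article defines the per-protocol set arm by arm. QT participants enter it if they "receive at least one telephone session and those in the WQ group who use the QUIT WMP for at least 20 days", where the second half of that quote is the first condition for WQ. The second WQ condition, joined by 'and', is that they "send more than 10 short messages in the QUIT WG".

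The section on the QT intervention describes a first session, a second session and up to three more after the quit date, so up to five. It says of the opening one: "The first session will focus on quitting history, motivation, self-efficacy, social support, and planning in advance of the quitting date". It also has counsellors try each participant at three times of day on three consecutive days per session.

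On the WQ side, Table 1 lists a mini-program function that records and displays days without smoking, and Table 2 recommends it in weeks 2 to 4. The week 3 group task in Table 2 is "Sharing quitting achievements picture in the online group", and the week 4 task is to share one's cessation experience there.

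The per-protocol analysis is introduced as an addition to the 'ITT' analysis. The same paragraph removes from the 'ITT' set anyone who uses no cessation service after randomisation.

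**The concern.** A per-protocol comparison gives up some of the protection of randomisation. What remains depends on the selection being similar in the two arms and not driven by the outcome, and both conditions are in doubt here.

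- **Unequal thresholds.** A QT participant qualifies after one call, which may be the planning call before any quit attempt. A WQ participant must be active on 20 of 28 days and must also post repeatedly.
- **Link to the outcome.** The four weeks in which WQ activity is counted run up to the 1-month endpoint. A participant who has relapsed has fewer quit days to record and less success to share, so abstainers are more likely to meet the WQ rule. The QT rule has no such link.

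Both features push toward WQ. At stake is how the supplementary result is read: an apparent WQ advantage could come from selection alone, and the plan does not say that the result is only supportive.

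**Working it through.** **The plan's own figure.** The Sample size section uses "significance level of 0.05 for a two-sided test", 90% power, 20% in QT, "an increase in abstinence rate of 15% in the WQ group compared with the QT group" (so 35%) and 20% dropout. With pooled variance:

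n = [1.960·√(2·0.275·0.725) + 1.282·√(0.20·0.80 + 0.35·0.65)]² / 0.15² = 184.1, so 185 per arm. Then 185/0.8 = 231.25, so 232 per arm and 464 in total.

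The arcsine formula gives 184 per arm, and 184/0.8 = 230, which is 460 exactly. The stated size reproduces. The point does not depend on it, but it supplies the 20% base rate, the 5% level and 230 per arm used below.

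**Thresholds as a share of what is scheduled.**
- QT: 1 of up to 5 sessions, or 20% of the longest schedule.
- WQ: 20 of 28 days, or 71%, plus more than 10 messages.

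**Who is left in each set.** If using no service in QT means having had no call, the 'ITT' set already excludes those participants, and the QT per-protocol rule removes almost nobody more. The WQ rule removes every WQ participant who falls short on days or on messages.

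**Size under no true effect.** The document gives no expected adherence and no link between engagement and abstinence, so these inputs are assumptions:
- true abstinence 20% in both arms
- share qualifying, a: 0.95 in QT; 0.3, 0.5 or 0.7 in WQ
- latent correlation ρ between engagement and abstinence: 0.2 to 0.5, the same in both arms

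Abstinence among those qualifying is P = Φ₂(Φ⁻¹(0.20), Φ⁻¹(a); ρ)/a, where Φ₂ is the bivariate normal distribution function. The numbers analysed are 0.95·230 = 218.5 in QT and 69, 115 or 161 in WQ. The chance of p<0.05 comes from the pooled two-proportion test.

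Worked case, a = 0.5 and ρ = 0.3: QT 20.7%, WQ 26.7%, difference 0.060. The standard error is 0.0483 under the null and 0.0495 otherwise. Then Φ[(0.0601 − 1.96·0.0483)/0.0495] = Φ(−0.70) = 0.24.

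| WQ qualifying | ρ | QT | WQ | OR | P(p<0.05) |
|---|---|---|---|---|---|
| 30% | 0.2 | 20.5% | 26.8% | 1.42 | 21% |
| 30% | 0.3 | 20.7% | 30.4% | 1.68 | 39% |
| 30% | 0.4 | 20.9% | 34.3% | 1.98 | 62% |
| 30% | 0.5 | 21.0% | 38.4% | 2.35 | 81% |
| 50% | 0.2 | 20.5% | 24.5% | 1.25 | 14% |
| 50% | 0.3 | 20.7% | 26.7% | 1.40 | 24% |
| 50% | 0.4 | 20.9% | 29.0% | 1.55 | 39% |
| 50% | 0.5 | 21.0% | 31.3% | 1.72 | 55% |
| 70% | 0.2 | 20.5% | 22.7% | 1.13 | 8% |
| 70% | 0.3 | 20.7% | 23.9% | 1.20 | 12% |
| 70% | 0.4 | 20.9% | 25.1% | 1.27 | 16% |
| 70% | 0.5 | 21.0% | 26.1% | 1.33 | 22% |

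Every cell exceeds the nominal 5%. Nine of the 12 are below 50%.

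**Second model.** Suppose all QT participants qualify and the odds of abstinence are 2 to 5 times higher in qualifying than in non-qualifying WQ participants. With 30% to 70% of WQ qualifying, the spurious difference is 3.0 to 19.6 points, and the chance of a significant result favouring WQ is 11% to 89%. If 90% of QT qualify and a call is equally prognostic, the difference is 2.1 to 18.0 points.

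**The case against.** Several points on the other side are sound.

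- **The analysis is supplementary.** The aim, the primary outcome and the sample size do not rest on it, and nothing in the text lets it confirm or replace the 'ITT' result. A reader might infer that it is there to rescue a failed primary result, but the document plans no such thing. It is also not the only further look at efficacy: subgroup analyses are planned, including by frequency and duration of service use.
- **The 20-day rule has a basis.** It equals the protocol's own reminder threshold of 5 days per week over 4 weeks, so it is a reasonable adherence rule for WQ alone. The fault is that QT has no counterpart.
- **Much WQ activity does not need abstinence.** The week 1 task is a daily screenshot in the group, about 7 messages. Week 2 discusses past failures. The smoking-reduction and diary functions serve people still smoking, and low users are reminded by telephone. This weakens the link with the outcome by an unknown amount, but the recording and sharing activities of the later weeks keep part of it.
- **The numbers rest on assumptions.** The share qualifying and the correlation are not in the document. That almost all QT participants would qualify is also an inference, though one supported by the repeated call attempts and the exclusion of non-users.

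None of this justifies or balances the unequal thresholds, and the document offers no reason for them.

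**Conclusion.** The point holds as a defect of a supplementary analysis that should be fixed. The per-protocol thresholds are unequal as written, and the WQ criteria are post-randomisation behaviours that partly follow from quitting, so the comparison can be expected to favour WQ with no true effect. Under the first set of assumptions the spurious gap runs from about 2 to 17 points. At its upper end it is larger than the 15-point design effect.

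A reader might go further and say that this analysis will show a WQ benefit whatever the truth. The figures do not support that: at the mild end (70% of WQ qualifying) the chance of p<0.05 is 8% to 22%. The direction of the bias is well founded; its size depends on adherence that is not yet known. The main analysis is unchanged by this defect. However, because its 'ITT' set also leaves out non-users, the plan as written has no analysis of all randomised participants against which to check the per-protocol result.

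**What to change.** 1. Drop the message-count criterion, and do not compare the arms in sets defined by unequal adherence thresholds.
2. Estimate the effect of adherence with a method that keeps the randomised comparison, for example a complier-average causal effect. Fix the adherence definition and the method's assumptions in advance.
3. If a per-protocol set is kept, define it in each arm as a comparable share of the sessions or days actually scheduled for that participant, and adjust for baseline FTND and cigarettes per day. This reduces the bias but does not remove it.
4. State that the per-protocol result is supportive only and cannot replace the analysis of all randomised participants, and report that analysis as well.

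Matching 71% of days with four of five calls would not be enough. Some QT participants may be scheduled fewer than five sessions, and equal percentages need not give equal selection. In the first model with ρ = 0.3 and no true effect, 40% of QT and 60% of WQ qualifying gives 28.4% against 25.2%, a bias toward QT.

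The cost is small. The Service usage data section already has call records and usage logs collected, so no new data are needed. The price is a smaller QT per-protocol set, or a less precise estimate, and a little more analysis work. The change should be made before any comparison by arm is seen.

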### Randomization and allocation

Participants will be randomized in a 1:1 ratio to the QT group or the WQ group using a block randomization method with randomly selected block sizes (4 or 6). This study is an open-label trial. A non-participating staff member will generate a randomization sequence via SAS 9.4 software which will be concealed using sealed opaque envelopes.

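### Subgroup efficacy falls under the unqualified P < 0.05 rule with no stated interaction test or exploratory status, so a uniform effect can easily look like a subgroup difference

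*Protocol article*

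**What the plan says.** The protocol article deals with subgroups in one sentence of its Statistical analysis plan section: "Subgroup analyses will assess the efficacy in participants with different demographics, baseline smoking characteristics, combined chronic diseases". The sentence goes on to add variables describing use of the intervention, and names multiple logistic regression as the method. That is also the method for the primary outcome.

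The section then closes with a single decision rule: "A two-sided *P* value of < 0.05 will be considered as statistically significant difference". It makes no exception for subgroups. The article contains no treatment-by-subgroup interaction term, no exploratory label, no multiplicity control and no list of factors or cut-points.

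The Sample size section sizes the trial for one overall comparison, assuming "an increase in abstinence rate of 15% in the WQ group compared with the QT group".

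This point concerns the baseline factors only. Subgroups defined by use of the intervention arise after randomisation and raise a separate problem.

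**The concern.** A subgroup analysis should ask whether the treatment effect differs between types of participant. The sentence instead asks whether WQ is efficacious in each type, and the rule lets a P value below 0.05 in any of them count as a significant result.

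Testing level by level can mislead in two ways:

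- If WQ works equally well for everyone, each level has less power than the whole trial. One level may then reach significance and the other miss it by chance, which invites the conclusion that WQ works only in one type of smoker.
- If WQ has no effect, every extra level is another chance of a false positive.

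The article hopes that WQ will narrow disparities between socioeconomic groups, and socioeconomic factors would plausibly be among the demographics. A false claim that only some smokers benefit could affect who is offered the service.

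**Working it through.** **Inputs from the article**

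- Sample size section: two-sided alpha 0.05, power 90%, QT abstinence 20%, WQ abstinence 20% + 15 points = 35%, dropout 20%, 460 participants (230 per arm).
- Randomization and allocation section: 1:1 allocation.

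**Assumptions, not in the article**

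- Independent two-level factors, each splitting the sample 50:50.
- An unadjusted pooled two-proportion z-test of WQ against QT in each level.
- 230 per arm analysed, since most losses are counted as smokers and stay in the denominator. A check uses 184 per arm (230 × 0.8).

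**The plan's own figure**

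n per arm = [1.96·√(2 × 0.275 × 0.725) + 1.282·√(0.20 × 0.80 + 0.35 × 0.65)]² / 0.15² = (1.238 + 0.798)² / 0.0225 ≈ 184.1, so 185. Dividing by 0.8 gives 232 per arm, 464 in total. The arcsine method gives 184, hence 230 per arm and exactly 460. The stated size is reproduced.

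**Power within one level (115 per arm)**

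z = [0.15 − 1.96·√(0.39875/115)] / √(0.3875/115) = (0.15 − 0.1154) / 0.0580 ≈ 0.60, so power is about 72%. The same formula gives about 95% for the whole trial at 230 per arm.

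**Uniform effect, one factor**

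P(significant in exactly one of two levels) = 2 × 0.72 × 0.28 ≈ 0.40.

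**No effect, one factor**

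P(at least one of two levels significant) = 1 − 0.95² ≈ 0.10.

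**Several factors**

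Levels of different factors share participants, so these tests are not independent and the probabilities were simulated (4,000 trials per setting). Ranges are across repeated runs.

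| Factors | Uniform 20% vs 35%: some factor significant in exactly one level | No effect: some level significant | Unadjusted interaction tests: some false positive |
|---|---|---|---|
| 1 | 40% | 9–10% | 5% |
| 2 | 56% | 17% | 9–10% |
| 3 | 62–64% | 21–22% | 14% |
| 5 | 71–73% | 28–31% | 22% |
| 8 | 79–80% | 37–38% | 31–33% |

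The last column is close to 1 − 0.95^F for F factors: 14%, 23% and 34% for 3, 5 and 8.

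**Sensitivity**

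- At 184 per arm, power in a half-sample level (92 per arm) falls to 63%. The uniform-effect column becomes 46–47% for one factor, 72% for three, 80% for five and 85% for eight.
- With 30:70 splits at 230 per arm, the one-factor figure rises to 48–50%.
- With no effect, the chance of a significant level reaches about 50% only near 15 factors.

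**The case against.** The strongest reply is that a journal article condenses a fuller plan. Factor lists, cut-points, interaction terms and exploratory status commonly sit in that plan, so their absence here proves nothing. That stands for the list and cut-points. It does not dispose of the point, because the article prints an aim (efficacy in each type of participant), a method and a significance rule without exceptions. A fuller plan would have to override what is printed.

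A reader might infer that the article commits to separate tests within each level. It does not say so. Logistic regression can carry an interaction term, and the sentence neither includes nor excludes one. Separate testing is the natural reading of the wording, and the figures above depend on it. Nor does the article say that a significant level will be contrasted with a non-significant one. That contrast is the error the wording invites, not a stated rule.

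A reader might also infer that a false subgroup claim is likely even if WQ works for no one. For three to eight factors the chance is about 21–38%. That is well above 5%, but not more likely than not.

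Nor is an interaction test a full cure. It holds the error near 5% per factor, but across factors it still errs in 14% to 33% of trials with three to eight factors. With no effect, that is only a modest improvement on level-by-level testing. The large gain is in the uniform-effect case.

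Finally, subgroups are not among the trial's aims or outcomes, and the trial recruits only in Beijing. A false claim about regions is therefore not a realistic consequence.

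**Conclusion.** The point holds in limited form. As printed, the plan judges baseline subgroup efficacy under the same unadjusted rule as the primary outcome, with no stated interaction test or exploratory status.

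If levels are tested one by one and the planned effect is uniform, a spurious pattern of benefit in one level only is more likely than not from two factors upward (56%). With no effect, the false-positive risk is several times the nominal 5% but stays below even odds for any plausible short list.

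The exact sizes rest on the assumed number of factors, their independence and 50:50 splits, and unadjusted tests; smaller analysed numbers or uneven splits make the uniform-effect problem worse. The primary test and the sample size are unaffected. This should be corrected, but it bears on secondary claims only.

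**What to change.** Replace the baseline part of the subgroup sentence with wording to this effect:

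- For each baseline factor on a pre-specified list, the primary logistic model will add the factor and a treatment-by-factor interaction.
- The interaction P value, and the odds ratio with 95% CI in each level, will be reported.
- Within-level P values will not be used to declare efficacy.
- All baseline subgroup results are exploratory and lie outside the 0.05 significance rule.

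The last item must not be dropped, because the interaction tests alone leave the error across factors uncontrolled.

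The cost is a few sentences in the plan and, for each factor, a model with the factor and its interaction added. The drawback is that interaction tests have low power in a trial sized for the overall effect, so few subgroup differences could be claimed.

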##### WQ modality-based treatment

The WQ modality integrated three WeChat app-based cessation services, including the QUIT WeChat mini program (WMP), the QUIT WeChat group (WG), and the QUIT WeChat official account (WOA). Screenshots of these services have been shown in our previous study [18]. They are developed based on the I-CET model and connected with each other [18]. Since the target population is smokers who plan to quit in the next month, the WQ modality is mainly aimed at the stages of preparation, action, and maintenance, which are focus on motivating to quit, building skills for coping with smoking cravings, and preventing relapse, respectively.

The QUIT WMP is an application function module embedded in the WeChat app [24] (similar to cessation apps [25–27]), which could assist smokers in developing the capacity to quitting smoking and motivating them to do so. It was developed based on the behavior change techniques (BCTs) [28], and smoking cessation treatment guidelines [10, 29]. The detailed description of its functions is shown in Table 1. In addition, the QUIT WMP will automatically send stage-matched short messages, articles or videos via the WeChat app to the users once a day for 4 weeks from the quit date. A list of weekly topics and examples of messages is shown in Table 2. It can be accessed by scanning a QR code (Additional file 2) or searching Chinese ‘Jie Yan You Dao’ in the WeChat app without downloading or installing [24]. The QR code and introduction video of the QUIT WMP will be sent to the participants via the WeChat app after allocation. To increase the participants’ adherence of using the QUIT WMP, daily usage reminders messages will be sent in the WeChat group. Moreover, we will download the participants’ usage data of the QUIT WMP every week, and remind those who use the program less than 5 days per week by telephone.

**Table 1 Tab1:** Detailed description of functions of the QUIT WeChat mini-program

Functions	Sub-functions	Description
Registration	Recording current smoking behavior	Record amount smoked, smoking duration, price of cigarettes, tar content of cigarettes, pattern of smoking behavior, etc
	Recording past history of quit attempts	Record number and duration of past quit attempts
	Testing the level of nicotine dependence	Provide a standardized test to help users assess their level of nicotine dependence
	Assessing quitting readiness	Assess motivation to quit and the stage of smoking cessation

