	Barrier identification and problem solving	Help users to identify the barriers (e.g. nicotine withdrawal symptoms, stress, etc.) that might make it harder to stay off cigarettes and provide personalized suggestions according to the barriers (e.g. how to deal with withdrawal symptoms, eliminate stress, and obtain social support, etc.)
	Strengthening ex-smoker identity	Encourage those who have quit smoking to construct a new identity as never smokers
	Preventing relapse	Provide users information about how relapses occur and to provide coping skills for preventing relapses
Medication reminder	Assessing medication(s) using experiences	Assess usage, side effects and benefits experienced of medication(s) that the smoker is currently using
	Setting a medication use plan	Set the daily time and amount of medication use
	Medication use reminder	Remind users to take medication on time
Additional supports	Quitline	Give information about tobacco quitline ([name]), and develop the “One Click Call” function
	Smoking cessation clinic	Provide online appointment of smoking cessation clinic
	Online consultation	Provide the link of QUIT WeChat group to obtain real-time online consultation
	Online self-help materials	Offer the link to QUIT WeChat official account to obtain online self-help materials for smoking cessation
Users Information	Quitting information	Such as duration of quitting and the number of attempts to quit
	Motivation to quit	Reason for quitting smoking
	Achievements	Virtual medals and accumulate points

**Table 2 Tab2:** The WQ^a^ modality-based treatment by week

Week	Stage	Topic	Example of messages automatically sent by the QUIT WMP^b^	Interventions in the QUIT WG^c^			
				**Group interventions**	**Topic discussion**	**Quit tasks**	**The QUIT WMP functions recommended to use**
Week 1	Preparation	Motivating to quit	Why do you want to quit smoking? Please write your reasons and put it where you can see it every day	Health hazards of smoking and benefits of quitting smoking	Why do I quit smoking?	Sending a screenshot of using the QUIT WMP in the online group every day	Reducing smoking Quitting diary
Week 2	Action	Setting a quit day	Please choose a date as the quit day, such as birthday, holiday, anniversary, etc	Facilitating a quit plan	Why did I fail to quit smoking in the past and how to deal with it this time?	Setting a quit day and announcing a quit declaration in the online group	Facilitating action plan Recording quitting Coping with cravings

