#### Other interventions

All participants will receive a 4-week supply of NRT gum by mail (300 pieces). The gum is FDA-approved Nicorette brand 2 mg nicotine mint gum (McNeil Sweden AB, Inc., Helsingborg, Sweden). Participants will be directed to use the gum as needed when they encounter situations or cues that tempt them to smoke, or in anticipation of such situations [38]. A smoking cessation material with a video link to the instruction of medication use will be mailed with the gum.

After receiving the allocation interventions for 4 weeks, participants in the QT group will receive reactive smoking cessation counseling via telephone for one year, and participants in the WQ group will also receive the reactive counseling via the WeChat group. Smoking cessation interventions other than the allocated intervention are prohibited during the study, such as bupropion, varenicline, electronic cigarettes and other mHealth-based tools, such as web, SMS texting, apps, etc.

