#### Service usage data

Service usage data will also be downloaded from the WeChat app and quitline platforms on a weekly basis during the intervention period. The QUIT WMP utilization metrics (registration, logins) will be extracted from host servers; participation in the QUIT WG (e.g., retention time and the number of messages sent) will be extracted. Telephone counsellors used a web-based tool to record the number, duration and content of calls.

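### Efficacy subgroups include gum compliance and service use, which arise after randomisation; the WQ-vs-QT effect by WeChat use cannot be estimated, and by gum use it may be biased

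*Protocol article*

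**What the plan says.** The protocol article, Statistical analysis plan, states: "Subgroup analyses will assess the efficacy in participants with different demographics, baseline smoking characteristics, combined chronic diseases, and use of intervention variables". It then spells out the last group as "use of intervention variables (including compliance of using NRT gum, frequency and duration of using WeChat- or quitline-based cessation services) using multiple logistic regression". Baseline and use variables share one sentence, one purpose (efficacy) and one model. The use variables are not marked as exploratory, within-arm or associational.

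Other sections show when and in whom these variables arise:

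- **Service use data:** "Service usage data will also be downloaded from the WeChat app and quitline platforms on a weekly basis during the intervention period". The WQ metrics are registration, logins, group retention time and messages; the QT metrics are the number, duration and content of calls.
- **Gum:** "All participants will receive a 4-week supply of NRT gum by mail (300 pieces", so compliance can exist in both arms.
- **QT service:** "Participants in the QT group will receive standard proactive quitline services".
- **WQ service:** "The WQ modality integrated three WeChat app-based cessation services".
- **Table 1:** the WQ mini program has a medication function that assesses use, sets a plan and will "Remind users to take medication on time". It also gives quitline information and a one-click call.
- **Other interventions:** cessation help outside the allocated arm, including other mHealth tools, is prohibited.

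**The concern.** A treatment-effect subgroup keeps the protection of randomisation only if its members could have been identified before allocation. Heavy users of a service, or participants who take their gum, are identified afterwards. The two arms deliver different services and prompt their use differently: QT counsellors make repeated call attempts, while WQ sends daily messages and telephones low users. The people who end up as high users may therefore differ between arms.

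At stake is the meaning of the subgroup odds ratios. As written, a contrast between non-randomised groups would be reported as efficacy. For WeChat use the contrast has no comparator at all.

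**Working it through.** **Plan's own figure.** The only related figure is the sample size of 460. With 20% vs 35%, two-sided 0.05 and 90% power, the pooled formula gives 185 per arm. Then 185/0.8 rounds up to 232 per arm, or 464 in total. The unpooled formula gives 181, then 227 per arm, or 454. With 230 × 0.8 = 184 per arm, power is 90.0%. The figure reproduces, and this point does not depend on it.

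**Step 1: timing.** Service use is logged during the four-week intervention, and gum is mailed as part of treatment. Both are post-randomisation.

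**Step 2: estimability by WeChat use.** Take the logistic model with columns 1, arm, use, arm × use. If WeChat use is 0 throughout QT, arm × use equals use in every row. The matrix has rank 3 with 4 columns, whether use is continuous or binary. The WQ-vs-QT effect among WeChat users is not identified.

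**Step 3: one high/low category across arms.** Calls and logins could be pooled as use of the allocated service, and the model would then fit. Assumed inputs, none from the article: a prognostic factor U ~ N(0,1); logit P(quit) = −1.4 + bU with no treatment effect; use driven by U plus N(0,1) noise, cut at a different level in each arm; 2,000,000 simulated subjects.

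| High users, WQ vs QT | b | OR, high users | OR, low users |
|---|---|---|---|
| 30% vs 30% | 0.5 or 1.0 | 1.00 | 1.00 |
| 30% vs 60% | 0.5 | 1.18 | 1.18 |
| 30% vs 60% | 1.0 | 1.37 | 1.40 |

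The true odds ratio is 1.00 throughout. The spurious effect appears only when the proportion of high users differs by arm.

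**Step 4: gum compliance.** Assumed inputs: U ~ N(0,1); logit P(gum) = −0.5 + U + r × arm; logit P(quit) = −1.6 + 0.8U + 0.5 × gum + e × arm. Here r is the effect of assignment on gum use and e is the direct WQ effect.

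| e | r | Gum use, WQ vs QT | Overall OR | OR, gum users | OR, non-users |
|---|---|---|---|---|---|
| 0 | 0 | 40% vs 40% | 1.00 | 1.00 | 1.00 |
| 0 | 0.3 | 46% vs 40% | 1.02 to 1.03 | 0.96 | 0.96 to 0.97 |
| 0 | 1.0 | 60% vs 40% | 1.10 | 0.89 | 0.88 |
| 0.6 | 0.3 | 46% vs 40% | 1.71 | 1.64 | 1.67 |
| 0.6 | 1.0 | 60% vs 40% | 1.83 | 1.52 | 1.53 |

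Ranges are variation between simulation runs. With e = 0, WQ does nothing once gum use is fixed, so the stratum value should be 1.00. The shortfall is selection: if WQ draws less motivated people into gum use, WQ users and WQ non-users are both less motivated on average than their QT counterparts.

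**Step 5: size against noise.** With about 115 per arm in a half-trial stratum and rates of 35% and 20%, SE(log OR) = √[1/(115 × 0.35 × 0.65) + 1/(115 × 0.20 × 0.80)] = √(0.0382 + 0.0543) = 0.30. The biases are ln 0.96 = −0.04 and ln 0.88 = −0.13.

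**The case against.** The strongest reply is that the wording on WeChat- or quitline-based services may mean each arm's own service, analysed within arm as dose-response. That model can be fitted, and the rank argument would not apply to it. The result would then be an association rather than efficacy, which is the word the article uses. On this reading the fix is mainly a matter of labelling, but it is still needed.

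The other objections limit how far the point reaches:

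- **Gum as a mediator.** A reader might infer that WQ certainly raises gum use. The article does not show this. The medication reminder is one function in Table 1, its plan is set by the user, and it is not among the functions Table 2 recommends week by week. Both arms receive the same gum and mailed instructions, and the article does not say what quitline counsellors tell callers about gum.
- **Reversed direction.** A reader might expect subgroup results to point the wrong way. In the simulations this happens only when WQ has no direct effect. With a 6-point difference in gum use the shift is small and far below sampling error. With equal use there is none.
- **Greater benefit in heavy users.** A reader might fear a false claim of this kind. In the gum simulations the two strata are nearly equal, and in the service-use cases shown high users never have the larger odds ratio.
- **Quitline use in QT only.** The one-click call makes some quitline contact possible in WQ, so use there need not be zero. It would still not match a proactive multi-call protocol.

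A condensed article may also leave interaction tests for baseline subgroups to the full analysis plan, so their absence is no fault. The choice of use variables as efficacy subgroups, however, is stated in the article itself.

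**Conclusion.** The point holds in this limited form. Gum compliance and service use are post-randomisation variables and should not define subgroups for WQ-vs-QT efficacy.

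- For WeChat use, the between-arm effect cannot be estimated, given that QT has no WeChat service.
- For quitline use, the arms are not comparable.
- For gum compliance, the contrast can be computed. It is open to bias if gum use is prognostic and differs by arm. Both conditions are plausible, and neither is established.

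The size is unknown because the article gives no usage rates. Under the assumed models the distortion runs from none (equal use) to an odds ratio of about 0.88 where 1.00 is correct (20-point difference in gum use). In the other direction it is 1.18 to 1.40 when high service use is 30% in WQ and 60% in QT. The sign depends on which arm has more users.

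The primary comparison and the sample size do not rest on these analyses. The plan should be changed, but the trial's main conclusion is not at risk from this point.

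**What to change.** In the Statistical analysis plan section, limit WQ-vs-QT efficacy subgroups to variables fixed at baseline: demographics, baseline smoking characteristics and chronic disease. Move gum compliance and the frequency and duration of service use to a separate sentence. State there that they will be reported within each arm as non-randomised associations with abstinence, and that no WQ-vs-QT odds ratio will be given by level of use.

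The cost is wording, plus some exploratory tables dropped or relabelled. No new data are needed, and the sample size does not change.
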